#### Participants

The study will consist of patients aged 18–75 years old who meet the inclusion criteria and are undergoing first-episode lumbar microdiscectomy for symptomatic lumbar disc prolapse in the participating private and public hospitals in Melbourne, Victoria, Australia during the trial period. Informed consent will be sought.

Inclusion Criteria.

#### Participants will be

Age 18–75 yearsSuffering from radiculopathy or radicular pain with concordant MRI evidence of lumbar disc herniation at L3/4, L4/5 or L5/S1

#### Exclusion criteria

Previous history of lumbar surgery, spinal infection or spinal fracture.

##### Treatment allocation

Patients will be randomised to one of two parallel treatment arms allocated in a 1:1 ratio. Sealed numbered envelopes containing electronically randomised group allocations and group specific post-operative activity instructions will be prepared prior to trial commencement. Following informed consent, a sealed pre-randomised envelope will be allocated by the study nurse to the patient and the patient label affixed to the envelope. The envelope will then be handed to the treating physiotherapist to be opened postoperatively. The study interventions are specifically detailed on this instruction sheet and will be read by the physiotherapist to the patient postoperatively. For both allocation groups, the study card instructions are discussed and reinforced by the treating physiotherapist. The physiotherapist also gives the patient the activity monitor and instructs them on how to use this. The patient will receive a copy of the instruction card to take home and is advised not to disclose their allocation group to medical staff or assessors. The physiotherapist is not involved in subsequent assessment of the patient.

Post-operatively both groups will be fitted with electronic monitoring devices, worn on either the thigh under clothing or carried in the pocket, that will record patient position (sitting/lying/standing) and activity (walking/running/cycling). The devices will be taken off when showering or bathing.

#### Control Treatment

Post-operative activity restrictions represent the traditional standard of care following lumbar microdiscectomy. As such the control group will be advised to follow post-operative activity restrictions for a period of one month following lumbar microdiscectomy. The control group will receive the following specific advice:

For the first one month following surgery:Avoid sitting for longer than 15–30 min in any two hour periodNo bending, lifting, twisting, pulling or pushing greater than 5 kgAvoid heavy domestic work such as vacuuming, laundry and making beds

And for the first two weeks following surgery:4.Avoid strenuous sexual activity

The restrictions detailed above reflect post-operative algorithms in current clinical practice. [unpublished data, [name] et al.].

#### Investigational treatment

The investigational treatment arm will be the group without sitting or other restrictions. They will be advised to return to normal activities with no restrictions placed on sitting, exercise, return to work, or other activities as soon as they feel ready.

### Outcomes

#### Primary endpoints

While there is no widely used definition of clinical success following lumbar microdiscectomy it is generally accepted that such a definition should take account of outcome measures such as physical function, disability and pain [9–11]. Intervertebral disc reherniation and reoperation are important considerations as potential primary endpoints. In SPORT[12] 20% of patients who underwent surgery rated their progress as less than a major improvement at one year yet only 6% had undergone reoperation. Thus, reherniation and reoperation alone do not account for the majority of unsatisfactory patient outcomes following lumbar discectomy. The use of a composite endpoint allows for the capture of multiple outcomes that influence the overall success of a clinical intervention while also allowing for increased statistical efficiency and efficient resource utilisation [13, 14].

As such the primary endpoint to be assessed in this trial consists of a composite of the following widely accepted outcome measures:18 point reduction in VAS lower back25 point reduction in VAS legs15 point improvement in ODI scoreAbsence of disc reherniation (defined as repeat surgery at the same level)No other secondary intervention (epidural or nerve root injection, medial branch block)

Using the above definitions of treatment success we would anticipate treatment success rates of ~70–90% in keeping with those reported in the literature [8, 15]. This allows the ability to detect a clinically significant difference in outcomes between the two groups (i.e. rates of clinical success) with smaller groups than required for the detection of differences in recurrence rates (i.e. event rate of “clinical success” of approximately 70–90% as opposed to herniation event rate of 5–10%).

Utilisation of the personal wearable electronic device will enable accurate assessment of patient adherence to the allocated post-operative care group.

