## Discussion

The longstanding practice of applying post-operative activity restrictions following lumbar spine surgery was based upon the hypothesis that such restrictions may reduce the risk of progressive instability or lumbar disc reherniation [5]. Furthermore, prolonged sitting has been suggested to decrease lumbar lordosis, increase spinal loading and muscle activity and contribute to accelerated disc degeneration and low back pain independent of previous operative intervention [19]. The randomised controlled trial of Bono et al. [7] demonstrated no significant difference in outcome measures between patients who observed two weeks or six weeks of activity restrictions though was underpowered to detect differences in reherniation rates. The only prior studies investigating the impact of removing post-operative restrictions reported no increased risk of reherniation or reoperation in patients not observing activity restrictions following lumbar discectomy surgery but these studies lacked a comparator group and their design was subject to potential bias [5, 6]. Modern lumbar discectomy is now minimally invasive and results in less tissue destruction, further undermining the hypothetical rationale for activity restriction. In a recent survey of Australasian Neurosurgeons, many advised either no sitting restrictions (22%) or sitting as comfort allows (40%) [unpublished data, [name] et al.]. However, the vast majority (84%) advised restricted lifting.

In an uncontrolled prospective cohort study [6] patients who did not observe post-operative activity restrictions returned to work earlier. Mean time to return to work in the cohort was 1.2 weeks. Currently extant recommendations suggest four to 16 weeks off work following lumbar discectomy surgery.

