### Activity monitoring/adherence

The activity monitor will monitor and record patient posture (i.e. lying, sitting or standing) and activity (walking, running or cycling) over the one month period following lumbar microdiscectomy. This device is sensitive to acceleration. The validation report described 90.8% correlation between activity monitor output and video analysis [20]. Data is recorded over the one month period on the stand-alone device and then transferred to the study computer.

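### The wearable is said to measure adherence to the allocated regimen, but it records one of the four restrictions on the card, and the per-protocol rule scores time in movement, which is not on the card

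*Protocol article*

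**What the plan says.** Under Primary endpoints, the protocol article says: "Utilisation of the personal wearable electronic device will enable accurate assessment of patient adherence to the allocated post-operative care group". The abstract makes a similar, less explicit claim: actual adherence to allocation will be monitored electronically. The Background is mixed. It first claims great reliability for observing adherence to sitting restrictions, then says the trial will be the first to track adherence to activity restrictions generally.

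Under Treatment allocation, both groups get a monitor "worn on either the thigh under clothing or carried in the pocket" and "that will record patient position (sitting/lying/standing) and activity (walking/running/cycling". The Activity monitoring/adherence section repeats these six categories and adds: "This device is sensitive to acceleration".

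Under Control Treatment, the card gives the restricted arm four instructions. The first begins "Avoid sitting for longer than" and sets a limit per two-hour period. The others concern bending, lifting, twisting, pulling or pushing above a stated weight; heavy domestic work; and, for the first two weeks only, strenuous sexual activity.

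Under Statistical analysis, intention-to-treat and per-protocol results will both be reported. Adherence is to be defined by two movement thresholds. Restricted patients above their threshold and sedentary unrestricted patients are excluded in one sensitivity analysis and cross-allocated in another.

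**The concern.** The stated claim covers adherence to the whole allocation, but the listed outputs contain nothing on load, trunk flexion, trunk rotation or type of task. A statistical analysis plan can choose thresholds for recorded data. It cannot recover lifting or bending data that the device never recorded. The gap therefore comes from what is collected and is not a detail that can be settled at the analysis stage.

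A second mismatch sits on top of the first. The adherence rule uses total movement, while the only card item the device can see is sitting. The rule therefore does not use the one relevant measurement that is available.

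What is at stake is the meaning of every analysis that depends on adherence status. The Non-Adherence section calls this assessment especially important, because the consent discussion may weaken adherence in the restricted arm. A per-protocol result could be read as the effect of observing activity restrictions when adherence to most of them is unknown.

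**Working it through.** The protocol gives no figure to reproduce on this point. The check sets the card beside the device outputs and then beside the adherence rule.

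**Step 1: card items (Control Treatment) against recorded categories (Treatment allocation; Activity monitoring/adherence).**

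| Card item | Recorded category? |
|---|---|
| Sitting limit | Yes: sitting |
| Bending, lifting, twisting, pulling, pushing | No: no load or trunk measure is described |
| Heavy domestic work | No: may appear as standing or walking, but cannot be told apart from permitted activity |
| Strenuous sexual activity (two weeks) | No |

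Count: 1 of 4 is recorded and 4 − 1 = 3 are not.

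**Step 2: the validation figure.** The 90.8% correlation in Activity monitoring/adherence is between monitor output and video analysis. It supports the six recorded categories and says nothing about the three unrecorded items.

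**Step 3: the adherence rule (Statistical analysis) against the card.** The rule counts a restricted patient as adherent when time in movement is below a sedentary level. Two cases follow:

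- A patient who lifts heavy loads but whose total movement stays below that level is classed as adherent, although the lifting instruction was broken.
- A patient who keeps to the sitting limit by walking a good deal can exceed the level and be classed as non-adherent, although no card item was broken.

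The converse also holds: long sitting keeps movement low, so a patient who ignores the sitting limit can be classed as adherent.

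**Step 4: context from the protocol's own survey (Discussion).** Of the surgeons surveyed, "the vast majority (84%) advised restricted lifting". On sitting, 22% set no restriction and 40% advised sitting as comfort allows: 22% + 40% = 62%. At most 100% − 62% = 38% set a firmer limit. Lifting advice is thus common in practice (84%, against at most 38% for a firm sitting limit), and it is among the items the device does not record.

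**Step 5: which analyses depend on this.** Per-protocol, exclusion and cross-allocation analyses all use adherence status. Intention to treat does not.

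**The case against.** The case on the other side has several parts.

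- *The claims are not uniformly broad.* The Background limits its reliability claim to sitting, and the Non-Adherence section says only that non-adherence may be determined from the device. The Statistical analysis section speaks of movement restriction. This is fair, but the Primary endpoints sentence is unqualified and the Background itself widens the claim. The passages need reconciling.

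- *The randomised comparison is sound.* Patients are randomised to advice and analysed by intention to treat, so a null result addresses the effect of the advice whatever patients lifted. This stands. A reader might infer that a null trial result could not be interpreted; the documents do not support that. Only the adherence-based readings are weakened.

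- *A lifter is not always misclassified.* A reader might infer that a restricted patient who lifts but sits little counts as adherent under any device rule. Under the stated movement rule, a busy patient may exceed the threshold and be classed as non-adherent. Misclassification is possible, not certain, and it runs in both directions.

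- *The count and the survey do not measure an effect.* The four items need not carry equal weight, one applies for only two weeks, and the survey is unpublished. It gives figures for sitting and lifting only, so it cannot show that lifting is the most widely used restriction of all. All of this stands.

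- *Self-report may already be collected, and is weak.* The Follow up schedule lists a current-situation questionnaire whose content is not shown, so the absence of such items cannot be established. The Background also criticises self-reported adherence as likely to bias. Both points argue against making self-report a condition of per-protocol status. Neither argues against collecting it as a supplement.

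**Conclusion.** The point holds. The protocol credits the device with a property that its listed outputs do not give it. One of four card items is a recorded category, and the adherence rule is built on time in movement, which is none of the four. The per-protocol, exclusion and cross-allocation analyses therefore cannot be described as showing the effect of adhering to the regimen. The intention-to-treat comparison of advice is unaffected.

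The conclusion assumes that the six listed categories are the device's full output, as both sections describe, and that no adherence measure outside this article covers the other items. If the unshown questionnaire does ask about lifting and housework, the data gap narrows. The over-broad claim for the device and the mismatch between rule and card would remain. How many patients would be misclassified cannot be estimated from the document. The change is worth making because the wording correction is free and alters what the adherence analyses can conclude.

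**What to change.** 1. Limit the claims in the abstract, Background and Primary endpoints to what the device records: posture and locomotion, and hence adherence to the sitting item.

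2. Reconcile the adherence measure in Statistical analysis with the card in Control Treatment by basing the device criterion on recorded sitting time. This assumes the stored data allow sitting to be totalled over the card's two-hour periods. The card states its limit as a range, so the analysis must say in advance how that range is applied. The unrestricted arm has no sitting limit to break, so the plan should say separately what the device data are meant to show there.

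3. Report device-based per-protocol results as adherence to that measured component only, and state that the device does not measure adherence to the lifting and domestic-work advice.

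4. Add a few self-completed items on lifting, bending and housework to the existing one-month online form. Use them descriptively or in a sensitivity analysis, not as a required condition for per-protocol status.

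The cost is rewording, one changed criterion and a few questions. The new items are self-reported, a weakness the Background itself notes. Because questionnaires are completed with help from a blinded investigator, both the completion and the storage of these items must be kept from blinded staff, including the study nurse.

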#### Secondary endpoints

Secondary endpoints will consist of the following surgical and functional endpoints.

Surgical endpoints:Incidence to 12 months post-operatively of disc reherniation requiring repeat surgery at the same levelIncidence to 12 months post-operatively of other parenteral pain management intervention such as epidural or nerve root injection, medial branch block for the primary illness, but excluding enteral or dermal analgesia (fentanyl patches, TENS machine or acupuncture).

Functional endpoints:VAS lower back change scoreVAS legs change scoreODI change scoreDays to return to work (including days to return to modified duties and to normal duties.)

For functional endpoints, magnitude of change from baseline, adjusted for baseline score will be compared between treatment groups. Additionally, the proportion achieving predefined success thresholds (change scores of 18 for VAS back, 25 for VAS legs and 15 for ODI) will be compared.

### Duration of treatment

Patients will be instructed to follow the post-operative advice- i.e. restrictions or no restrictions for a period of one month. Monitoring of adherence using wearable electronic activity monitors (Activ8, 2 M Engineering, Netherlands) will be for 1 month.

### Follow up schedule

With the assistance of a blinded investigator, participants will complete online outcome questionnaires preoperatively, the day following surgery, and at home at one, three, six and 12 postoperative months.

Questionnaires will include:VAS lower back painVAS leg painODICurrent situation/patient satisfaction questionnaireSF-12/EuroQol (EQ-5D)(quality of life questionnaire)

Patients will receive standard post-operative trial-blinded neurosurgical outpatient review at approximately 30–60 days following surgery at trial sites. Teleconsultation will occur at the three, six and 12 months. Patients will only receive further neurosurgical outpatient review if clinically indicated.

### Participant timeline

The participant timeline is illustrated below in Table 1.

**Table 1 Tab1:**
[figure not shown]
Participant timeline template for schedule of enrolment, interventions and assessment

#### Randomisation and allocation concealment

Randomisation of treatment protocol to sequentially numbered envelopes was performed by an electronic randomisation tool. Sealed envelopes will be sequentially assigned immediately following consent. The treating physiotherapist is given a sealed envelope by the blinded study nurse upon randomisation. This contains the patients assigned group and the appropriate post-operative instructions. This is opened by the physiotherapist post operatively.

#### Blinding

Blinding will be universal from consent till surgery. Postoperatively the physiotherapist will open the envelope and inform the patient of their assigned group. The study nurse will complete all assessment of patients at each time point and will be blinded as to patient randomisation throughout the study. Participants will be instructed not to inform study staff regarding their allocation. Surgical staff will remain blinded throughout the trial.

#### Non-Adherence

Patient data will be analysed on an intention to treat basis. Non-adherence to post-operative activity protocol may be determined by analysis of recorded activity from the wearable device. This will be especially important in light of the trial explaining to participants as part of consent procedures the clinical uncertainty regarding movement restriction, which may result in poor adherence in the group subsequently assigned to restriction.

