Bono et al. [7] recently published the first report of a randomised controlled trial investigating post-operative activity restrictions following lumbar discectomy. This trial compared post-operative protocols consisting of short (two weeks) and long (six weeks) periods of activity restriction following lumbar discectomy. The authors observed no significant difference in outcome as assessed by Visual Analog Scale (VAS) back or leg pain or Oswestry Disability Index (ODI). Disc reherniation rates differed between the groups observing short (11%) and long (7%) periods of activity restriction. This difference did not achieve statistical significance or translate into an appreciable difference in clinical outcome. However, the authors noted the study was underpowered to detect a significant difference in disc reherniation rate and calculated approximately 800 patients per arm would be required to achieve sufficient statistical power.

All previous studies on post-operative restrictions following lumbar discectomy have relied on self-reported adherence to mobility restrictions. Non-adherence is a well-recognized phenomena in spine surgery trials with non-adherence rates in SPORT approximately 40% at one year [8]. Such outcomes are likely to be biased. Contemporary wearable electronic devices that can accurately record the patient’s position (i.e. sitting/standing) enable empirical observation of patient adherence to a regimen of sitting restrictions with great reliability. This trial will be the first to track post-operative adherence to activity restrictions following lumbar discectomy and the impact of adherence on outcomes.

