#### Sample size

As detailed earlier one randomised controlled trial investigating the role of post-operative activity restrictions in outcome following microdiscectomy has recently been reported [7]. The authors recruited 108 patients and noted disc reherniation rates of 11% in the 2-week restriction group and 9% in the 6-week restriction group. Previous studies have indicated a reherniation rate ranging from 2 to 18% [16]. Annual reported reherniation rates have been closer to 4–5% in large series [8, 17, 18]. The authors of the randomised controlled trial calculated it would be necessary to have 800 patients in each arm in order to detect a statistically significant difference in disc reherniation rate and that this may not be feasible. We are in agreement with this assessment.

Reported rates of clinical success for lumbar discectomy vary widely dependent on the criteria. Using the criteria detailed in our composite primary outcome we would anticipate a clinical success rate within the broad range reported in the literature of approximately 70–90%.

In determining the power of this study, we assume that approximately 80% of patients will meet the definition of treatment success. The calculation of sample size can be based upon a threshold of a 20% difference in treatment success as clinically significant (i.e. 80% success vs. 64% success). In order to have 80% power to detect a 20% difference in the binomial outcome of treatment success defined at *p* = 0.05 the sample size calculated would be 78 patients per group. If we allow for an approximately 30% drop-out rate, this will bring the calculated sample size to 105 patients per group for a total of 210 patients in the trial.

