#### Statistical analysis

Hazard of reherniation and of parenteral analgesia will be compared by treatment arms. Efficacy will be defined as 1 minus hazard ratio of active vs restricted arms. Efficacy less than absolute delta (see sample size) will be deemed equivalent. Change from baseline adjusted for baseline in functional scores will be compared across treatment arms. Magnitude difference will be compared using ranksum (Mann-Whitney-U) test.

Analysis will report both intention to treat and per protocol results. Per protocol adherence to treatment will compare time in movement by treatment arm using t-test allowing for differential variance**.** Time in movement should differ between arms. Two thresholds will be defined a priori – a sedentary level below which will be considered adherent to movement restriction, and an activity level above which non-restriction will be deemed to have occurred. These thresholds will be used to define adherence. In sensitivity analysis we will examine impact on trial outcomes of excluding those subjects allocated to restriction who moved above this threshold and those unrestricted who were sedentary. We will also conduct sensitivity analysis by cross allocating such subjects.

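### The sample size makes no stated allowance for poor adherence to restriction and does not say whether 80% vs 64% is the effect of the advice or of full adherence

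*Protocol article*

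**What the plan says.** All references are to the protocol article.

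- **Non-Adherence.** Data are analysed by intention to treat. Because consent explains the clinical uncertainty about restriction, the authors foresee a process "which may result in poor adherence in the group subsequently assigned to restriction". No rate is given.
- **Background.** The only non-adherence figure comes from another trial: "Non-adherence is a well-recognized phenomena in spine surgery trials with non-adherence rates in SPORT approximately 40% at one year".
- **Sample size.** The target is "i.e. 80% success vs. 64% success". The calculation is stated as "In order to have 80% power to detect a 20% difference", and "the sample size calculated would be 78 patients per group". A drop-out allowance of about 30% takes this to 105 per group, 210 in total. Adherence is not mentioned.
- **Statistical analysis.** Efficacy, one minus the hazard ratio, is judged equivalent when it lies below a delta taken from the Sample size section. Intention-to-treat and per-protocol results are both reported. On the monitor data the section says "Time in movement should differ between arms", with a t-test between arms. Two adherence thresholds are to be set in advance, with sensitivity analyses that exclude or cross-allocate non-adherent patients.
- **Background and Question.** The trial asks whether no restriction is inferior. A finding of no difference is meant to let future patients return quickly to normal activity.

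**The concern.** Patients who ignore the restriction advice stay in the restricted arm under intention to treat. Drop-out inflation replaces patients who leave the analysis. It does nothing for patients who remain but behave like the other arm. If 80% vs 64% describes restricted against unrestricted behaviour, the difference actually analysed will be smaller than the one used for sizing.

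The direction matters. Dilution pulls the arms together, and a finding of no difference is the one that would change practice here. The protocol says movement should differ between arms but attaches no consequence to the equivalence statement if it does not.

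**Working it through.** **Inputs.** From Sample size: success 80% and 64%, power 80%, p = 0.05, 78 per group before drop-out. From Treatment allocation: 1:1.

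**Assumptions.** The restricted arm has the 80% (the protocol does not say which arm does). The test is two-sided unless noted (sidedness is not stated). A share f of the restricted arm does not adhere, and those patients have the unrestricted success rate. f runs from 0 to 40%. The upper end matches the figure in Background, which comes from a different trial at one year.

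**Step 1: reproduce the 78.** For two proportions with pooled null variance,

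n = [1.960·√(2·p̄(1−p̄)) + 0.842·√(p1(1−p1) + p2(1−p2))]² / (p1−p2)².

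With 0.80 and 0.64 (p̄ = 0.72) this gives 122.4, so 123 per group, or 97 one-sided. The 78 is not reproduced. Two other readings come close:

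- 80% vs 60%, two-sided, unpooled: (1.960 + 0.842)² × (0.16 + 0.24) / 0.20² = 78.5.
- Non-inferiority with 80% in both arms, a 16-point margin and one-sided 0.05: (1.645 + 0.842)² × 0.32 / 0.16² = 77.3, rounded up to 78.

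**Step 2: power at full adherence.** With 78 per group, the null standard error is √(2 × 0.72 × 0.28 / 78) = 0.0719 and the alternative standard error is √((0.16 + 0.2304) / 78) = 0.0707. Then (0.16 − 1.960 × 0.0719) / 0.0707 = 0.27, and Φ(0.27) = 61%. This loss of 19 points from the stated 80% occurs before any non-adherence.

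**Step 3: dilution, detection reading.** The restricted-arm rate becomes 0.80 − f × 0.16, compared with 0.64. The third row repeats this with 60% in place of 64%.

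| Non-adherence f | 0% | 10% | 20% | 30% | 40% |
|---|---|---|---|---|---|
| Restricted-arm success (target 80 vs 64) | 80.0% | 78.4% | 76.8% | 75.2% | 73.6% |
| Power, 80 vs 64, n = 78 | 61% | 51% | 42% | 33% | 25% |
| Power, 80 vs 60, n = 78 | 78% | 68% | 57% | 46% | 35% |
| Power, 80 vs 64, one-sided, n = 78 | 72% | 64% | 54% | 45% | 36% |
| Power, 80 vs 64, n = 105 (no drop-out) | 74% | 64% | 53% | 42% | 32% |

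A full 30% drop-out from 105 leaves 105 × 0.70 = 73.5 per group, so 78 is slightly generous.

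**Step 4: dilution, non-inferiority reading.** Suppose full restriction truly gives 80% vs 64%, so the true deficit sits on the 16-point margin. The analysed deficit is d = 0.16 × (1 − f), and the chance of declaring non-inferiority is Φ((0.16 − d)/SE − 1.645), with unpooled SE at 78 per group.

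- f = 0: 5%.
- f = 20%: d = 0.128, SE = 0.0724; 0.032/0.0724 − 1.645 = −1.20, giving 11%.
- f = 40%: d = 0.096, SE = 0.0738; 0.064/0.0738 − 1.645 = −0.78, giving 22%.

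This step applies the margin to the composite endpoint. The article words its equivalence rule for hazards and refers to Sample size for delta, so it is an illustration rather than the article's own test.

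**The case against.** The strongest reply is that the trial randomises advice. Intention to treat estimates the effect of that advice with ordinary non-adherence included. The article calls 80% vs 64% a clinically significant threshold and does not present it as a full-adherence contrast. A reader might infer that the sample size treats the control arm as fully restricted, but the text does not say so. This stands: the dilution figures are conditional on that reading.

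A reader might also infer that the protocol predicts poor adherence, or expects 40%. It says only that adherence may be poor. The 40% is from another trial at one year, whereas the advice here lasts one month. Giving every non-adherer the unrestricted success rate also allows no credit for partial restriction.

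The article does plan for non-adherence: one month of device monitoring in both arms, a between-arm movement comparison, thresholds set in advance, per-protocol results, and exclusion and cross-allocation analyses. These would show whether the arms behaved alike. They do not restore the randomised comparison, because they select or reassign patients on behaviour after randomisation. Nor does any of them limit when equivalence may be stated. A t-test also sets no minimum separation.

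Finally, an interpretation rule might be left to an analysis plan that is not shown. That is fair for its numerical value. The equivalence statement, however, is made in the article without condition.

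**Conclusion.** The point holds in a limited form. The article raises poor adherence in one arm, fixes intention to treat, lists drop-out as its only allowance, and leaves open what 80% vs 64% represents.

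The shortfall has two separate parts. The drop from 80% to 61% power is arithmetic and has nothing to do with adherence. The further loss, about 8 to 10 points for each 10% of non-adherence at 80% vs 64%, arises only if that contrast assumes full adherence and non-adherers take the unrestricted rate. If 78 came from a non-inferiority calculation, the harm is a higher chance of wrongly declaring no restriction non-inferior rather than lost power. If 80% vs 64% is already the effect of the advice, neither dilution figure applies, but the question of interpretation remains.

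It would go too far to say that a null result would tell us nothing about the safety of no restriction. It would still bear on whether giving the advice changes outcomes. What it could not support, without shown separation between the arms, is a conclusion about restriction itself.

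**What to change.** 1. **Sample size.** Keep 210 patients. State whether 80% vs 64% is the effect of the advice as followed or of full adherence, and which arm has the 80%. Correct the power at full adherence, then restate intention-to-treat power (or, if non-inferiority is intended, the false non-inferiority risk) over a stated range of restricted-arm non-adherence, for example 10% to 40%.
2. **Statistical analysis.** Make any conclusion of equivalence or non-inferiority about restriction itself conditional on a pre-specified between-arm separation in monitored activity or sitting time, reported with a confidence interval. If the separation is not met, limit the conclusion to the effect of giving the advice.

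The cost is wording in the protocol or analysis plan. The monitor data are already to be collected, and no patients or visits are added. The downside is a less favourable stated power and possibly a narrower conclusion.
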